# ICEAGE (Incidence of Complications following Emergency Abdominal surgery: Get Exercising): study protocol of a pragmatic, multicentre, randomised controlled trial testing physiotherapy for the prevention of complications and improved physical recovery after emergency abdominal surgery

**DOI:** 10.1186/s13017-018-0189-y

**Published:** 2018-07-03

**Keywords:** Emergency surgery, Abdominal surgery, Complications, Physiotherapy, Breathing exercises, Postoperative pulmonary complication, Pneumonia, Ileus, Rehabilitation, Patient education

## Abstract

**Background:**

Postoperative complications and delayed physical recovery are significant problems following emergency abdominal surgery. Physiotherapy aims to aid recovery and prevent complications in the acute phase after surgery and is commonplace in most first-world hospitals. Despite ubiquitous service provision, no well-designed, adequately powered, parallel-group, randomised controlled trial has investigated the effect of physiotherapy on the incidence of respiratory complications, paralytic ileus, rate of physical recovery, ongoing need for formal sub-acute rehabilitation, hospital length of stay, health-related quality of life, and mortality following emergency abdominal surgery. We hypothesise that an enhanced physiotherapy care package of additional education, breathing exercises, and early rehabilitation prevents postoperative complications and improves physical recovery following emergency abdominal surgery compared to standard care alone.

**Methods:**

The Incidence of Complications following Emergency Abdominal surgery: Get Exercising (ICEAGE) trial is a pragmatic, investigator-initiated, multicentre, patient- and assessor-blinded, parallel-group, active-placebo controlled randomised trial, powered for superiority. ICEAGE will compare standard care physiotherapy to an enhanced physiotherapy care package in 288 participants admitted for emergency abdominal surgery at three Australian hospitals. Participants will be randomised using concealed allocation to receive either standard care physiotherapy (education, single session of coached breathing exercises, and daily early ambulation for 15 min) or an enhanced physiotherapy care package (education, twice daily coached breathing exercises for a minimum 2 days, and 30 min of daily supervised early rehabilitation for minimum five postoperative days). The primary outcome is a respiratory complication within the first 14 postoperative hospital days assessed daily with standardised diagnostic criteria. Secondary outcomes include referral for sub-acute rehabilitation services, discharge destination, paralytic ileus, hospital length of stay and costs, intensive care unit utilisation, 90-day patient-reported complications and health-related quality of life and physical capacity, and mortality at 30 days and at 1 year following surgery.

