## Methods/design

### Trial objectives

The primary objective of the Incidence of Complications following Emergency Abdominal surgery: Get Exercising (ICEAGE) trial is to estimate the effectiveness of physiotherapy on the incidence of PPC, including pneumonia, in patients following emergency open abdominal surgery.

Secondary objectives are to estimate the possible effect physiotherapy may have on prolonged postoperative ileus incidence, rates of referrals for formal sub-acute rehabilitation services, discharge destination, hospital length of stay (LOS) and costs, readiness to discharge from hospital, intensive care unit (ICU) LOS and readmissions, and rate of change to physical function and quality of life (QOL) whilst in hospital and at 90 days, and 1-year mortality.

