#### Secondary/exploratory trial outcomes

In hierarchical order:Referral by the surgical team or other allied health professional within the first 14 postoperative days for additional acute-ward physiotherapy rehabilitation, sub-acute hospital rehabilitation, or community-based rehabilitation. On receipt of a referral, or by the 14th postoperative day if referral not received, a blinded senior physiotherapist will review the participant’s current medical record and adjudicate for the requirement for rehabilitation services.Discharge destination from the acute hospital ward (home, rehabilitation facility, nursing home, or other hospital);Hospital LOS in days. This is defined as continuous days spent in any type of inpatient hospital service (i.e. acute care, sub-acute rehabilitation, or time at another hospital) from the day of admission for acute condition to the day of discharge to community. Hospital days will be sub-categorised into acute and sub-acute;Incidence of a prolonged postoperative ileus (PPOI) anytime from the fourth to the 14th postoperative hospital day. A PPOI is defined if two or more of the following criteria are met on or after the fourth postoperative day [30]: (i) nausea or vomiting, (ii) inability to tolerate an oral diet over last 24 h, (iii) absence of flatus over the last 24 h, (iv) abdominal distension, and (v) radiologic confirmation. The day which PPOI is first diagnosed is the day of PPOI onset for purposes of time-to-event analysis.Diagnosis of pneumonia defined as the presence of new CXR infiltrates along with at least two of the following: temperature > 38 °C, dyspnoea, cough, and purulent sputum, altered respiratory auscultation, and white cell count > 14,000/ml or leukopenia < 3000/ml on any day within the first 14 postoperative hospital days;Recovery of physical function and QOLi)Rate of change of the Modified Iowa Level of Assistance [31] (mILOA; Additional file 1) score over four measures taken second daily from the first postoperative day and a final score on the day of acute-ward discharge. The mILOA consists of four mobility tasks (supine to sitting on the edge of the bed, sit to stand, walking, and negotiation of one step), which are graded according to the level of assistance required, use of gait aid, and the distance that can be walked. Data will be extracted from the medical and physiotherapy records to score;ii)Rate of change in handgrip strength (kg) measured using a handheld dynamometer over four postoperative measures within the first 14 days. Measures will be taken at least 2 days apart;iii)Rate in change of the EuroQual QOL score [32] (EQ-5D; Additional file 2); measures to be taken directly from the patient over two consecutive measures separated by 48 h, within the first five postoperative days, and at 90 days following surgery;iv)Health-related QOL using World Health Organisation Disability Assessment Schedule V2 [33] (WHODAS; Additional file 3) change from self-rated status in the week prior to surgery, to day of discharge from acute care, and at 90 days following surgery;v)Physical capacity using Self-Assessment of Physical Activity Questionnaire [34] (SAQ; Additional file 4) from self-rated capacity regarding the week prior to surgery to 90 days following surgery;vi)Time in hours from end of operation to time able to achieve ambulation greater than 1 min;vii)Time in days from end of operation to achieve ambulation greater than 10 min;ICU LOS in days;Unplanned ICU admission during acute hospital stay;Mortality—in-hospital, 30 and 90days, and at 1 year;Sepsis within the first 7 days according to the Sequential Organ Failure Assessment (SOFA) for ICU patients and quick-SOFA for ward patients [35];Time in days to discharge from physiotherapy as determined daily using the Post-Operative Physiotherapy Discharge Scoring Tool [18] (Additional file 1);Time in days to readiness for hospital discharge within the first 14 postoperative days defined by standardised scoring criteria [36];Patient reported complications at 90 days using a standardised semi-structured interview [16];Hospital costs for the admission episode of care supplied by the participating centres’, or health departments’, costing data for each participant’s admission episode.

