##### Secondary outcomes

Binomial outcomes including rehabilitation referrals, pneumonia, PPOI, unplanned ICU admissions, patient-reported complications, and mortality will be analysed using multivariate robust random effects Poisson generalised linear regression.Time-to-event binomial outcomes (e.g. PPC, pneumonia, PPOI, achievement of ambulation goals of 1 and 10 min; and hospital and ICU LOS; and mortality) will be compared by estimating hazard ratios using Cox proportional hazards regression, with and without covariate adjustment where necessary and graphically illustrated using Kaplan-Meier methods.Measures involving estimation of rate of change over time (QOL and functional capacity) will be analysed using repeated-measures mixed effects linear regression or ordered logistic regression for rank-ordered scale measures.Hospital costs will be compared using mixed effects linear regression. Log transformation of highly skewed cost data will be performed. Depending on the adequacy of the data for purposes of economic analysis, a cost-utility may be conducted.

All outcomes will be analysed on an intention-to-treat basis. An intention-to-protocol sensitivity analysis will be performed by identifying as a separate group participants who received more than 80% of planned protocol sessions as per group allocation. Other planned sensitivity analyses will be made according to age (> 65), surgery type (colorectal, upper gastrointestinal, other), preoperative self-reported physical capacity, and gender. Sensitivity of outcome estimates to missing data will be evaluated using multiple imputations. All analyses will be performed using Stata MP2 V14 (StataCorp, College Station, TX, USA).

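### In-hospital mortality is compared between arms although its window closes at discharge, which the treatment may bring forward

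*Protocol article*

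**What the plan says.** Under Secondary/exploratory trial outcomes, the protocol article lists its secondary outcomes "In hierarchical order". Mortality is the ninth of 14 items and reads "Mortality—in-hospital, 30 and 90days, and at 1 year". Three of its four time points are fixed windows; the in-hospital one is not.

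Under Statistical methods, Secondary outcomes, mortality is among the binary outcomes: "patient-reported complications, and mortality will be analysed using multivariate robust random effects Poisson generalised linear regression". The next sentence also names it among the outcomes for Cox regression. No time point is exempted from the binary comparison.

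The Trial objectives include "discharge destination, hospital length of stay (LOS) and costs, readiness to discharge from hospital" among the effects to be estimated, so discharge timing is something the treatment may alter. In the outcome list, referral for rehabilitation, discharge destination and length of stay are the first three items. Length of stay is defined there as "continuous days spent in any type of inpatient hospital service", which covers sub-acute rehabilitation and time at another hospital. The mortality item is not tied to that definition or to the acute stay.

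The time points are listed more briefly elsewhere. The abstract has "mortality at 30 days and at 1 year following surgery" and the Trial objectives have "quality of life (QOL) whilst in hospital and at 90 days, and 1-year mortality".

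**The concern.** A binary comparison of deaths is fair when every participant has the same period in which a death can count. Thirty-day, 90-day and 1-year mortality meet that condition. In-hospital mortality does not: each participant's window closes on the day of discharge, after randomisation, and the trial is set up to see whether the intervention moves that day.

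If the enhanced package speeds recovery and patients go home sooner, some deaths that would have been counted as in-hospital in the control arm occur after discharge in the intervention arm and drop out of the count. The risk ratio then favours the intervention with no life saved. This is a bias, so a larger sample would not remove it.

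The missing definition makes matters worse. If in-hospital means the acute stay, transfer to sub-acute rehabilitation also closes the window, and rehabilitation referral is the top-ranked secondary outcome. An arm with more transfers would then have the shorter window, so even the direction of the bias can depend on which definition is used.

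**Working it through.** **Plan's own figure.** The article states no figure for mortality or for stay by arm. Its sample size concerns the primary outcome: for 20% v 8%, two-sided 0.05 and 80% power, n = [1.96√(2 × 0.14 × 0.86) + 0.8416√(0.20 × 0.80 + 0.08 × 0.92)]² / 0.12² = 130.1, so 131 per group and 262 in all, as stated. Nothing here touches it.

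**Inputs.** From the article: 288 participants in two arms, so 288/2 = 144 per arm. Assumed, because the article gives none of them:
- 30-day mortality of 10% in both arms, with death times T = 30 × Beta(0.9, 1.6) days in both arms, so survival is identical; deaths after day 30 are ignored
- stay S log-normal, log-SD 0.7, median 8 days in one arm and 10 or 12 in the other
- a factor k by which the stay of patients who will die exceeds that of others; k = 1 means stay is unrelated to dying

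**Formula.** In-hospital mortality = 0.10 × P(T ≤ k × S).

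| k | median 8 d | median 10 d | median 12 d | ratio 8 v 10 | ratio 8 v 12 |
|---|---|---|---|---|---|
| 1 | 4.76% | 5.51% | 6.14% | 0.86 | 0.78 |
| 2 | 7.12% | 7.83% | 8.34% | 0.91 | 0.85 |
| 3 | 8.34% | 8.86% | 9.21% | 0.94 | 0.91 |

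**Deaths per 144.**
- k = 1: 144 × (0.0551 − 0.0476) = 1.1 and 144 × (0.0614 − 0.0476) = 2.0
- k = 2: 144 × (0.0783 − 0.0712) = 1.0 and 144 × (0.0834 − 0.0712) = 1.8
- k = 3: about 0.8 and 1.3

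The true ratio is 1.00 in every cell.

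**Effect on the test (k = 1, normal approximation).**
- 8 v 10 days: standard error √(2 × 0.05135 × 0.94865 / 144) = 0.0260; shift 0.0075/0.0260 = 0.29; chance of a significant result favouring the shorter stay P(Z > 1.96 − 0.29) ≈ 5%
- 8 v 12 days: standard error 0.0268; shift 0.0138/0.0268 = 0.52; chance ≈ 7%

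Both compare with a nominal 2.5% in that direction.

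**Second set of assumptions.** With a constant hazard within 0–30, 30–90 and 90–365 days, mortality of 10%, 13% and 20% at those times, log-SD 0.6 and k = 1:
- median 14 v 12 days: ratio 0.88 (7.7 v 6.8 deaths per 144)
- 14 v 10 days: ratio 0.75 (7.7 v 5.8)
- 20 v 14 days: ratio 0.77 (10.1 v 7.7)

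Varying 30-day mortality from 5% to 15% leaves the ratios at 0.74 to 0.88. The difference runs from about 0.4 deaths (3.8 v 3.4) to 3.5 (15.2 v 11.7).

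**The case against.** The strongest reply is that the effect is small and the safeguard is already in the plan. Mortality is a low-ranked item under a heading that includes the word exploratory. The three fixed windows stand beside the in-hospital figure, so a reader who sees a difference in hospital and none at 30 days would suspect the cause. This stands as a limit on the damage. It does not make the in-hospital comparison fair.

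The size rests on assumed figures, and k = 1 is unrealistic: it has 45% of 30-day deaths occurring after discharge at a median stay of 10 days (5.5% of 10% in hospital). Patients who are dying tend to stay, and the ratio then moves towards 1. This also stands, and is why the range for k = 2 and 3 is given.

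If in-hospital follows the broad definition used for length of stay, transfer from the acute ward would not close the window. That would narrow the problem, but the article does not say so, and discharge to the community would still end the count. Blinding of doctors and discharge coordinators does not help either, because faster recovery brings discharge forward whether or not staff know the allocation.

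Two stronger readings are tempting. A reader might infer that the abstract, objectives and outcome list contradict each other on when mortality is measured. They do not: the abstract says only what the secondary outcomes include, the objectives are a summary, and every time point in either appears in the outcome list. A reader might also infer a multiplicity defect from four time points with none designated. Under assumed rates the chance of at least one nominal p < 0.05 is about 12%, but for an exploratory item that is not by itself a defect, and the choice of a lead time point and model can be left to an analysis plan that is not shown.

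**Conclusion.** The point holds for in-hospital mortality alone. Read together, the outcome list and the Statistical methods plan a between-arm binary comparison whose observation window the treatment can shorten and whose end is undefined. With identical survival, the apparent risk ratio is 0.78 to 0.86 in the main scenarios if stay is unrelated to dying, and about 0.85 to 0.94 if dying patients stay two to three times longer. That is about 2 deaths or fewer per 144; longer stays and higher mortality could take it to about 3.5 where stay is unrelated to dying. All of these figures depend on assumed mortality and stay, and the bias appears only if stay does differ between arms.

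The fixed-window mortality outcomes do not share this bias. The primary outcome and the sample size are unaffected.

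**What to change.** - Base between-arm mortality comparisons on the windows already planned: 30 days, 90 days and 1 year.
- Report in-hospital deaths by arm as a descriptive count, without a test, and state whether the window is the acute stay or the full inpatient stay used for length of stay.
- As an editorial matter, bring the time points in the abstract and the Trial objectives into line with the outcome list.

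No new data are needed. The cost is that one pre-specified, low-ranked comparison becomes descriptive while the trial is running: recruitment began in June 2015 and was expected to finish in late 2018. The change should be recorded as a dated amendment made blind to results. That is feasible, since Trial monitoring says that outcome differences are not examined at the interim analysis and Blinding keeps analysts and statisticians masked.

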**Discussion:**

The morbidity, mortality, and fiscal burdens following emergency abdominal surgery are some of the worst within surgery. Physiotherapy may be an effective, low-cost, minimal harm intervention to improve outcomes and reduce hospital utilisation following this surgery type. ICEAGE will test the benefits of this commonly provided intervention within a methodologically robust, multicentre, double-blinded, active-placebo controlled randomised trial.

**Trial registration:**

ACTRN 12615000318583. Registered 8 April 2015

**Electronic supplementary material:**

The online version of this article (10.1186/s13017-018-0189-y) contains supplementary material, which is available to authorized users.

## Background

Globally, millions of people every year require urgent time-critical emergency abdominal surgery to resolve potentially catastrophic small bowel obstructions, gastrointestinal tract perforations, haemorrhage, invasive cancerous tumours, blunt force/penetrative trauma injuries, and peritonitis [1]. Emergency surgery accounts for approximately 11% of total surgical cases in the USA yet disproportionately can contribute to half of all surgical deaths and a third of all complications [2]. Postoperative outcomes following emergency abdominal surgery are generally poorer when compared to elective surgery. The most common serious complication after emergency abdominal surgery is a postoperative pulmonary complication (PPC) with an incidence rate of 20–50% [3–5]. Emergency surgery is the single greatest risk factor for a PPC, much greater than the risk attributed to other types of surgery and existing patient comorbidities [5]. The consequences of developing a PPC are serious with doubled health costs [6], longer hospital stay [5, 7], and higher mortality [5, 7, 8]. Understandably, efforts to improve postoperative outcomes following emergency abdominal surgery are strongly advocated [9].

Promising findings of reduced morbidity and mortality following the introduction of multidisciplinary perioperative care bundles, including increased physiotherapy [10, 11], are yet to be confirmed in randomised controlled trials. The size of the contribution of each individual treatment component within a care bundle also limits interpretation of findings. It is unknown whether physiotherapy can independently improve outcomes after emergency abdominal surgery.

Although the provision of physiotherapy to emergency abdominal surgery patients is ubiquitous in high-income countries [12], no clinical trials exist that have investigated the effect of physiotherapy on PPCs and overall recovery in this high-risk, high-care burden cohort over and above standard care [13].

## Methods/design

### Trial objectives

The primary objective of the Incidence of Complications following Emergency Abdominal surgery: Get Exercising (ICEAGE) trial is to estimate the effectiveness of physiotherapy on the incidence of PPC, including pneumonia, in patients following emergency open abdominal surgery.

Secondary objectives are to estimate the possible effect physiotherapy may have on prolonged postoperative ileus incidence, rates of referrals for formal sub-acute rehabilitation services, discharge destination, hospital length of stay (LOS) and costs, readiness to discharge from hospital, intensive care unit (ICU) LOS and readmissions, and rate of change to physical function and quality of life (QOL) whilst in hospital and at 90 days, and 1-year mortality.

### Trial design

ICEAGE is a pragmatic, multicentre, parallel-group, randomised controlled trial. It is patient and assessor blinded, and powered for superiority. Eligible patients will be randomly assigned via concealed allocation into one of two physiotherapy treatment arms (Table 1). The control group will receive standard care physiotherapy from the first postoperative day consisting of education on prevention of complications with upright positioning, ambulation, and breathing exercises; a single deep breathing and coughing (DB&C) coaching session; and no more than 15 min of supervised ambulation once daily until a threshold score is met to discharge from this service. The intervention group will receive an enhanced physiotherapy care package from the first postoperative day consisting of (i) education on prevention of complications with upright positioning, ambulation, and breathing exercises; (ii) at least twice daily coached DB&C for the first two postoperative days; and (iii) at least 30 min of supervised early rehabilitation daily for the first five postoperative days. The mode of ambulation and respiratory physiotherapy will be standardised for both groups. The difference between groups will be (1) additional reminders and education as necessary for performance of independent exercises, (2) longer duration of ambulation and/or provision of individualised rehabilitation exercises, and (3) increased number of coached DB&C sessions (see Fig. 1 for the ICEAGE trial CONSORT diagram).

**Table 1 Tab1:** TIDieR descriptions of ICEAGE interventions

TIDieR criterion	Control	Intervention
Item 1. Brief name: provide the name or a phrase that describes the intervention	Standard care: ‘talk, walk, breathe’	Enhanced physiotherapy care: ‘talk more, exercise more, breathe more’
Item 2 a) Describe any rationale, theory essential to the intervention	After emergency abdominal surgery the most common cause of morbidity and mortality is a postoperative pulmonary complication (PPC). Postoperative physiotherapy is routinely provided in intensive care units and surgical wards across Australia in an effort to prevent respiratory complications and enhance physical recovery after this major surgery type. Despite ubiquitous provision of this service, the effectiveness of postoperative physiotherapy is unknown.	Treatment components: ‘Talk more’: Repeated education sessions and reminders are allowed to be provided at the discretion of the physiotherapist. It is possible that more education will lead to greater motivation and increased independent performance of breathing and walking exercises.
Item 2 b) Describe goal of the elements essential to the intervention	Treatment components: ‘Talk’: The patient is informed of their risk of postoperative complications due to surgery and prolonged bed rest impairing their lungs and muscles. Education aims to inform, motivate, encourage, and inspire participation in exercises as prescribed. A booklet provides a written record of what was verbally taught. ‘Walk’: Early ambulation away from the bedside after surgery may prevent complications and physical decline after surgery. ‘Breathe’: Breathing and coughing exercises increase lung volumes, prevent postoperative atelectasis, improve gas exchange, clear stagnant secretions, and prevent postoperative pulmonary complications.	‘Exercise more’: The goal is to provide at least double the amount of physical activity daily. Daily physical activity will comprise of both ambulation and functional bed/chair/standing exercises. It is possible that there is a dose-dependent relationship with physical activity after surgery. Additional supervised physical activity early following surgery may hasten physical recovery and prevent complications more effectively. ‘Breathe more’: The goal is to provide at least four times the amount of coached breathing exercises in the first 2 days after surgery. It is possible that more breathing exercises performed early after surgery results in a greater risk reduction in the incidence of PPC.
Item 3. What (materials): describe any physical or informational materials used in the intervention, including those provided to participants or used in intervention delivery or in training of intervention providers.	Participant information materials: A booklet containing written and pictorial information regarding PPC and their potential prevention with early ambulation and breathing exercises to consolidate the learnt knowledge from verbal education and training. Intervention providers: Familiarisation with protocol prior to treating intervention participants. Badge cards containing the treatment protocol Template for documentation of treatment delivery Data entry sheets with further details of protocol	Participant information materials: As per control Intervention providers: As per control
Item 4. What (procedures): describe each of the procedures, activities, and/or processes used in the intervention, including any enabling or support activities	‘Talk’: once off Patients will have a single face-to-face education session following surgery with their physiotherapist. Patients will be educated on the benefit of walking and breathing exercises to prevent complications and improve recovery after surgery. Participants will be educated on the effect of surgery and bedrest to their lungs and muscles, and the benefit of walking and breathing exercises to prevent complications and improve recovery after surgery. Participants will be encouraged to perform the taught breathing exercises independently every hour during the day until they are walking at least 5 min, four times a day. Participants will also be strongly encouraged by their treating physiotherapist to sit upright, sit out of bed, walk away from their bedside (if safe to do so), or march on the spot beside their bed, as many times as they can during the following days to aid in the prevention of PPCs Participants will be provided with an education booklet. This booklet contains written and pictorial information about abdominal surgery, expected types of pain management, medical lines and drains, postoperative recovery process, and how to prevent postoperative respiratory complications with early ambulation and self-directed breathing exercises. The breathing exercises are prescribed within with the recommended prescription of reps and sets.	‘Talk more’: at least once, then as often as required As per the control group. In addition, intervention group participants will receive extra reminders and prompts during the first five postoperative days to perform the prescribed rehabilitation and breathing exercises independently. Pragmatically, the number of additional education sessions and the use of exercise diaries and instruction sheets will be at the discretion of each treating physiotherapist based on their clinical experience and the individual needs of the intervention group participant.
	‘Walk’: once daily ambulation only, < 15 min Initiation—as soon as practical after surgery Duration—no more than 15 min of total work time Frequency—once daily until a threshold score is met Intensity—rating of perceived exertion > 3/10, breathing deeper than at rest. Type—continuous activity for a minimum 1 min aiming for up to 15 min continuous as patient can tolerate. Allowable to train in intervals with work/rest ratio of 1:1 Mode—ambulation only. At every session the participant will be progressed sequentially through the protocol stages aiming to achieve a walking time of at least 10-min, but no more than 15-min. Successful ambulation is defined as continuously marching on the spot beside the bed or walking away from the bedside for more than 1 min. If a participant is unable to participate in upright ambulation, then no other non-ambulation exercises will be provided that day.	‘Exercise more’: once daily, ambulation and exercises, > 30 min Initiation—as soon as practical after surgery Duration—at least 30 min of total work time Frequency—once daily for at least the first 5 postoperative days and then until a threshold score is met Intensity—rating of perceived exertion > 3/10, breathing deeper than at rest. Type—continuous activity for a minimum 1 min aiming for as long as patient can tolerate. Allowable to train in intervals with work/rest ratio of 1:1 Mode—functional exercise programme starting with ambulation as per the control group protocol aiming for at least 15 min and if possible to at least 30 min of walking. If walking time is less than 30 min, non-ambulatory physical activity is continued to be provided until the minimum 30 min of activity time is achieved (not including rest periods). Physical activity is provided in a sequential step-down process starting with the highest activity possible and moving to less intense. These exercises consist of chair- or bed-based progressive low resistance, high repetition, lower and upper limb exercises of three–four sets as prescribed by the treating physiotherapist based on the individual patient’s requirements and functional ability. If a participant is unconscious or acutely unwell, functional electrical stimulation of muscles and/or passive movements of limbs can be used as a physical activity.
	‘Breathe’: once off coached session Participants will receive a single physiotherapy coached deep breathing and coughing (DB&C) session within the first 2 days following surgery, or once the ward physiotherapist considers a patient conscious enough to understand and participate in this session. Physiotherapists will treat patients in upright sitting either in a bed or in a chair. The coached DB&C exercises will consist of two sets of 10 slow-flow breaths to maximum inspiratory capacity with two to three inspiratory sniff breath-stacking manoeuvres at the end of each deep breath followed by a 3- to 5-s breath hold. Each set of 10 breaths are followed by three coughs, or a forced expiratory technique with an open glottis called a ‘huff’, with a small firm pillow, or suitable substitute, pressed over on the abdominal incision to support the wound and to encourage greater expiratory force. The treating physiotherapist will have the discretion to place hands on the patient’s chest wall during the coaching sessions to provide tactile feedback of performance. Total prescribed dosage of DB&C exercises is 20 breaths and six forced expiratory efforts every hour. The participants were encouraged to perform these every hour during the day until they were ambulant out of bed at least four times a day, for a minimum of 5 min at a time. No other prophylactic respiratory physiotherapy interventions or reminders to perform the taught DB&C exercises will be provided by the physiotherapist, this includes, but is not limited to, the following: manual or ventilator hyperinflation or recruitment manoeuvres in ventilated patients, manual techniques, positive expiratory pressure devices, incentive spirometers, or non-invasive ventilation.	‘Breathe more’: at least four coached sessions in the first 2 days: As per the control group. Additionally, intervention group participants will receive at least three additional physiotherapist-coached DB&C sessions in the first two postoperative days. At least four sessions will be provided in total. Beyond the second day additional, coached DB&C can be provided at the discretion of the treating physiotherapist if they consider the patient incapable of performing exercises unsupervised or they consider the patient requires additional respiratory exercises to prevent a PPC.
Item 5. Who provided: for each category of intervention, provider (for example, psychologist, nursing assistant), describe their expertise, background, and any specific training given	Qualified physiotherapists of varying experience levels at three different hospitals: new graduates, senior physiotherapists, and consultant level physiotherapists. An allied health assistant can deliver the ambulation protocol once this is deemed safe to do so by the treating physiotherapist.	Qualified physiotherapists of varying experience levels at three different hospitals: new graduates, senior physiotherapists, and consultant level physiotherapists. All sessions will be conducted by a physiotherapist (not an allied health assistant) until at least the fifth postoperative day unless the supervising physiotherapist is confident that an assistant or participant will undertake the rehabilitation programme exactly as prescribed for the minimum 30 min.
Item 6. How: describe the modes of delivery (such as face to face or by some other mechanism, such as internet or telephone) of the intervention and whether it was provided individually or in a group	Face-to-face, individual sessions	Face-to-face, individual sessions
Item 7. Where: describe the type(s) of location(s) where the intervention occurred, including any necessary infrastructure or relevant features	Inpatient hospital wards, patient bedsides at three government-funded, university affiliated, teaching hospitals Hospitals include a sub-regional secondary referral hospital, a regional primary referral hospital, and a metropolitan primary referral hospital.	Inpatient hospital wards, patient bedsides at three government-funded, university-affiliated, teaching hospitals. Hospitals include a sub-regional secondary referral hospital, a regional primary referral hospital, and a metropolitan primary referral hospital.
Item 8. When and how much: describe the number of times the intervention was delivered and over what period of time including the number of sessions, their schedule, and their duration, intensity or dose	See item 4	See item 4
Item 9. Tailoring: if the intervention was planned to be personalised, titrated or adapted, then describe what, why, when, and how	No tailoring	‘Talk’—Extra education sessions can be provided by physiotherapist as necessary based upon their clinical judgement and the requirements of the patient. ‘Exercise more’—Physiotherapist can incorporate specific functional exercises to target identified individual physical impairments, within the exercise protocol as long as the exercises comply with the goal intensity, duration, and type. ‘Breathe more’—Physiotherapist can provide more DB&C exercise sessions, in addition to the minimum of four coached sessions, in response to clinical judgement of risk and respiratory vulnerability.
Item 10. Modifications: If the intervention was modified during the course of the study, describe the changes (what, why, when, how)	N/A	N/A
Item 11. How well (planned): if intervention adherence or fidelity was assessed, describe how and by whom, and if any strategies were used to maintain or improve fidelity, describe them	Planned interim analysis of provision of ambulation programme to ensure that in > 80% of patients ambulation duration is no more than 15 min and provided until discharge criteria is met	Planned interim analysis of provision of exercise programme to ensure that in 80% of patients exercise duration is at least 30 min and provided for a minimum of five postoperative days/sessions.
Item 12: How well (actual): if intervention adherence or fidelity was assessed, describe the extent to which the intervention was delivered as planned	The trial will be amended or ceased for futility if there are critical failures to recruitment rates, breaches to protocol, or minimal treatment separation between groups.	The trial will be amended or ceased for futility if there are critical failures to recruitment rates, breaches to protocol, or minimal treatment separation between groups.

*Abbreviations: PPC* postoperative pulmonary complications, *DB&C* deep breathing and coughing

